#### Part B

Patients admitted with a primary diagnosis of non-ST elevation myocardial infarction will be recruited from the medical and cardiology wards at Cambridge University Hospitals NHS Foundation Trust. Patients may continue to receive trial treatments if they are transferred to the local interventional centre at Royal Papworth Hospital. Participants will be given at least 24 hours to review the patient information sheet prior to formal consent. Dosing should commence within 8 days of screening. All visits and blinding procedures will be the same as part A. However, in part B, a total of 32 patients will be recruited, eight patients in each of the four dosing groups (drug:placebo ratio of 6:2). A sentinel approach to dosing will also be employed in each group. After a blinded safety review of the first two patients, the remaining cohort will be randomly allocated to study treatments as shown in figure 3. The visit schedule for each patient is the same as part A (figure 1).

**Figure 3 F3:**
[figure not shown]
Trial design for each group in part B. There are a total of four dose levels in part B.

### Dose-escalation strategy

The first group of patients in part A will receive 0.3×10^6^ IU of aldesleukin daily. Thereafter, a blinded review of patient data by the blinded Trial Management Group (TMG) including review of AEs, blood results, ECGs, clinical records and, where possible, drug pharmacodynamics and pharmacokinetics. The TMG will be composed of an experienced, accredited early phase lead physician (LILACS chief investigator), a research physician/scientist, a research nurse, trial coordinator and an unblinded study statistician (for the purposes of data analysis). All data presented by the unblinded statistician to the TMG will be in an aggregated format to preserve the blind for the other TMG members. This is consistent with the commercial standard for such early phase trials in industry. The dose in the second group will be determined after this review, and the same process will be followed in each of the following groups. The maximum dose increments allowed by the protocol between groups will be double the previous dose and capped to a maximum 3.0×10^6^ IU.

A robust set of specific and general withdrawal criteria, as well as objective stopping criteria have been put into place to maintain the safety:risk benefit, in particular due to the risk of capillary leak syndrome.

Following completion of part A, an unblinded independent Data Monitoring Committee (DMC) will review all available safety data, together with any other analyses that the committee may request. The DMC will be composed of an independent group of clinical researchers with suitable experience in experimental medicine and early phase clinical trials. These researchers are independent from the trial team and have not been involved in the setup or running of this clinical trial. They will determine whether it is safe to progress to part B, based on available safety and pharmacodynamic data provided by the unblinded statistician. After this analysis, the dose in each group will be determined based on the review of ongoing patient data by the TMG, as in part A previously. The protocol mandates that the maximum dose used in part B will not exceed that of part A. DMC will be governed by a charter set up a priori and signed up by all members prior to the commencement of the trial (see supplementary file 2).

10.1136/bmjopen-2018-022452.supp1Supplementary file 1

### Outcome measure

#### Part A

The primary outcome will be the safety of IL-2 in patients. This will be assessed through:A review of AEs and SAEs, and concomitant medications.Changes in safety bloods (electrolytes (sodium, potassium and urea), bone profile (calcium and phosphate), serum creatinine, liver function tests (alanine transaminase, aspartate transaminase, alkaline phosphatase, bilirubin and gamma glutamyl transferase (GT)), thyroid function tests (thyroid stimulating hormone), blood glucose, full blood count and differential, and clotting (prothrombin time and activated partial thromboplastin time).Twelve-lead ECG and cardiac monitoring changes (arrhythmias, ischaemic changes and QTcB).Vital observations (blood pressure, heart rate, respiratory rate, peripheral oxygen saturation and temperature).Echocardiogram changes at baseline and follow-up.

Exploratory endpoints will include:Change in the mean circulating Treg level measured by fluorescence activated cell sorting (FACS) analysis following treatment with IL-2, over the 5 days of the treatment period.Change in cardiac biomarker measurements including hs-CRP, troponin I, IL-6 and b-type natriuretic peptide) from analysed blood samples.Change in lymphocyte subsets measured by FACS analysis.Pharmacokinetic analysis of IL-2 levels.

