### Use of IL-2 in clinical trials to date

The first report of effective IL-2 therapy in human cancer trials was published in 1985.^28^ The trial patients in that study were placed on dose-escalated IL-2 regimens, of up to approximately 120 million IU (MIU). Associated with these high IL-2 doses were side effects such as capillary leak syndrome (which is characterised by a loss of vascular tone and extravasation of plasma proteins and fluid into the extravascular space, ultimately resulting in hypotension, tachycardia, dyspnoea and pulmonary oedema) and kidney and liver damage (both characterised by increased serum creatinine and bilirubin levels, respectively) 29.

The use of low dose IL-2 to expand Treg cell populations in autoimmune and alloinflammatory conditions has been previously explored and published in human clinical trials. In these studies, patients received at least 1 dose of IL-2 ranging from 0.3×10^6^ IU to 3.0×10^6^ IU. In two studies of 12 and 21 healthy volunteers, respectively, there were minimal adverse events (AEs), consisting mainly of grade 1 injection site reactions. No cardiovascular AEs were noted.^30 31^ In one phase I/IIa study, 24 patients with diabetes mellitus were recruited and given a maximum dose of 3.0×10^6^ IU daily for 5 days. The authors found that IL-2 was well tolerated at all doses, with no serious adverse events (SAEs). However, there was a dose–response relationship for non-serious AEs. The most common AEs in the treatment phase were injection-site reactions and an influenza-like syndrome.^32^ In a later trial of 40 indivisuals with type 1 diabetes, the authors found that doses of aldesleukin were well tolerated at all doses, with no SAEs reported. The majority of participants had an expected AE at the injection site consisting a non-itchy, local (1–5 cm), non-painful erythematous rash that resolved on average by day 10.^33^ No cardiovascular AEs were reported in either study. Low dose IL-2 has also been used in 38 patients with systemic lupus erythematosus (SLE)^26^ who are considered to have a higher risk of coronary artery disease and therefore cardiac events.^34^ However, no SAEs were observed while injection site reactions and influenza-like symptoms were observed in 13.2% and 5.3% of patient, respectively.^26^

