	Exclusion criteria	Current presentation with cardiogenic shock (systolic blood pressure <80 mm Hg, unresponsive to fluids or necessitating catecholamines), severe congestive heart failure and/or pulmonary oedema. Known active bleeding or bleeding diatheses. Known active infection requiring antibiotic treatment. Severe haematological abnormalities (haematocrit <30% and platelet cell count of <100 × 10^3^/μL and white cell count <4 × 10^3^/μL). Known malignancies requiring active treatment or follow-up (however, patients with current/a history of localised basal or squamous cell skin cancer are not excluded from participation in this trial). Known heart failure with impaired LV function (LV EF<45%). Hypotension (systolic BP <100 mm Hg, DBP <50 mm Hg) at screening. Uncontrolled hypertension (>160/100 mm Hg) at screening. History of recurrent syncope (electrocardiographic history suggestive of arrhythmia syncope (eg, bifascicular block, sinus bradycardia <40 beats per minute in absence of sinoatrial block or medications, pre-excited QRS complex, abnormal QT interval, ST segment elevation leads V1 through V3 (Brugada syndrome), negative T wave in right precordial leads and epsilon wave (arrhythmogenic right ventricular dysplasia/cardiomyopathy)). Known hepatic failure or abnormal LFTs at baseline (ALT >2 × ULN). Elevated total bilirubin levels, (TBL >1.5 × ULN) and alkaline phosphatase, ALP (ALP >1.5 × ULN), at baseline. Acute kidney injury or chronic kidney disease at stage >3B (eGFR <45 mL/min/1.73 m^2^). Respiratory failure. Known hyperthyroidism or hypothyroidism. History of drug-induced Stevens Johnson syndrome, drug reaction with eosinophilia and systemic symptoms (DRESS syndrome) or toxic epidermal necrolysis. History of recurrent epileptic seizures in the previous 4 years; repetitive or difficult to control seizures, coma or toxic psychosis lasting >48 hours. If known diabetic, uncontrolled diabetes defined as HbA1c >64 mmol/mol. Average corrected QT interval >450 ms using Bazett’s formula using triplicate ECGs (or >480 ms if bundle branch block). Known chronic active hepatitis (B or C). Known HIV infection. Current infection possibly related to recent or ongoing immunosuppressive treatment. Known autoimmune disease requiring active immunosuppressive therapy. History of organ transplantation. Any oral or intravenous immunosuppressive treatment including prednisolone, hydrocortisone or disease-modifying drugs such as azathioprine, interferon-alpha, cyclophosphamide or mycophenolate. (Other immunosuppressive therapies should be discussed with PI. Inhaled or topical steroids are permissible). Known pregnancy at screening or visit 2 (where applicable). Ongoing lactation. Inability to comply with trial procedures. Current participation in other interventional clinical trials. Contra indication to interleukin (IL)-2 treatment or hypersensitivity to IL-2 or to any of its excipients. Unwillingness or inability to provide written informed consent for participation. Any medical history or clinically relevant abnormality that is deemed by the principal investigator/delegate and/or medical monitor to make the patient ineligible for inclusion because of a safety concern.

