### Stopping criteria

Dose-escalation stopping criteria will be met if two patients within a trial group experience any combination of: a SAE defined as possibly, probably or definitely related to the trial drug (ie, it is a SAR), an adverse event that is severe and at least possibly related to the trial drug or any of the objective stopping criteria detailed box 1. The following will then occur:Box 1Objective stopping criteria triggering a Data Monitoring Committee safety review of dose escalationQTcB >500 ms (or >530 ms if baseline QTcB=450–480 ms) OR QTcB change from baseline >60 ms (based on an average of triplicate electrocardiogram (ECGs)).Acute pulmonary oedema or congestive heart failure.Symptomatic systolic BP <90 mm Hg and/or diastolic blood pressure (BP) <60 mm Hg OR persistent symptomatic systolic BP 80–90 mm Hg for >15 mins OR severe hypertension (as defined by BP >180/120 mm Hg).ST-elevation myocardial infarction (STEMI) occurrenceAtrial fibrillation with rapid ventricular response >150/min, supraventricular tachycardia or bradycardia that requires treatment or is recurrent or persistent.Sustained ventricular tachycardia or ventricular fibrillation.Any patient who develops doubling of creatinine.Systemic hypersensitivity reaction that cannot be attributed to an identifiable cause.If a life-threatening infection is confirmed clinically with a positive microbiological test.Signs suggestive of hepatic failure including encephalopathy, increasing ascites, signs of coagulopathy, liver pain and/or tenderness on palpation, hypoglycaemia presumed to be secondary to liver failure and active GI bleeding. Withdrawal also if alanine aminotransferase (ALT)>3 ULN.Seizure activity, coma, severe lethargy or somnolence.Risk of respiratory insufficiency requiring intubation.

Dosing will be immediately discontinued for the patients experiencing the event.Dosing will be halted for all other patients currently in the treatment period of the trial (ie, patients receiving treatment in the same group).A safety review by the independent DMC will be conducted to determine how to proceed with the trial.Any further single instances of the events outlined above for the same group will trigger a further DMC safety review.Any patients who have their dosing discontinued will be withdrawn from the trial.

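### The QT part of the primary safety outcome is named only as Bazett QTcB, so if aldesleukin raises heart rate, part of any QTcB change by dose or against placebo could be a rate effect

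*Protocol article*

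**What the plan says.** The Outcome measure section of the protocol article, Part A, makes safety the primary outcome. Its ECG item lists "arrhythmias, ischaemic changes and QTcB". Part B takes over the same safety and tolerability endpoint. The next item in the Part A list covers "Vital observations (blood pressure, heart rate, respiratory rate, peripheral oxygen saturation and temperature", so heart rate and temperature are recorded, but nothing links them to the QT reading.

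The same correction is used elsewhere. Table 1 excludes patients in both parts by "Average corrected QT interval >450 ms using Bazett’s formula using triplicate ECGs", with a higher limit for bundle branch block. Box 1 under Stopping criteria uses an absolute QTcB limit and "QTcB change from baseline >60 ms". No second correction appears in the article.

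On the drug's effects, the section on use of IL-2 in trials to date says of a diabetes study at up to 3.0×10^6 IU daily: "The most common AEs in the treatment phase were injection-site reactions and an influenza-like syndrome". For high-dose cancer treatment it describes capillary leak as "ultimately resulting in hypotension, tachycardia, dyspnoea and pulmonary oedema".

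**The concern.** A corrected QT is meant to show repolarisation with the effect of heart rate taken out. Bazett does this only if QT is proportional to the square root of RR. If the true relation is flatter, QTcB over-corrects at faster rates and under-corrects at slower ones. A treatment that changes heart rate then moves QTcB even when repolarisation is unchanged.

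This matters because QTcB is part of a primary safety outcome that will be read by dose. ECGs are also among the data the Trial Management Group (TMG) reviews before setting each next dose, and the Data Monitoring Committee (DMC) reviews the safety data before Part B. A rate rise that grew with dose could look like a QTc rise that grew with dose. A rate fall could partly hide a real one. Subtracting placebo removes only rate changes common to both arms. It does not remove one caused by the drug.

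**Working it through.** **Plan's own figures.** The article gives QT limits but no expected QT, heart rate or change in either, so there is no stated figure to reproduce. Every rate and baseline QTc below is an assumption, shown as a range.

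**Inputs.** Correction: Bazett (Outcome measure, Part A). Change limit in Box 1: 60 ms. Assumed cube-root QTc: 400 to 420 ms. Assumed starting rate: 60 or 70 bpm. Assumed rises: 10, 20 and 30 bpm.

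**Formula.** With RR = 60/HR in seconds, QTcB = QT/RR^(1/2) and QTcF (Fridericia) = QT/RR^(1/3). Hold QTcF fixed, so that repolarisation does not change. Then QT = QTcF × RR^(1/3), and

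QTcB = QTcF × RR^(1/3 − 1/2) = QTcF × (HR/60)^(1/6).

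At QTcF 420 ms this gives QTcB of 420.0 at 60 bpm, 430.9 at 70, 440.6 at 80, 449.4 at 90 and 457.3 at 100.

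**Apparent QTcB change (ms) with no repolarisation change**

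| Heart rate (bpm) | QTcF 400 ms | QTcF 420 ms |
|---|---|---|
| 60 to 70 | +10.4 | +10.9 |
| 70 to 80 | +9.2 | +9.7 |
| 60 to 80 | +19.6 | +20.6 |
| 70 to 90 | +17.6 | +18.4 |
| 60 to 90 | +28.0 | +29.4 |
| 70 to 100 | +25.1 | +26.4 |

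The ranges are therefore about 9 to 11 ms for 10 bpm, 18 to 21 ms for 20 bpm and 25 to 29 ms for 30 bpm. Read in reverse, the same figures show how far a rate fall would lower QTcB.

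**Does this depend on the cube-root model?** Take an assumed linear relation instead, QT = QTc − 154(1 − RR). From 60 to 80 bpm RR is 0.75, so QT is 400 − 38.5 = 361.5 ms or 420 − 38.5 = 381.5 ms.

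- QTcB: 361.5 × (80/60)^(1/2) = 417.4, a change of +17.4 ms; 381.5 × (80/60)^(1/2) = 440.5, a change of +20.5 ms.
- QTcF: 361.5 × (80/60)^(1/3) = 397.9, a change of −2.1 ms; 381.5 × (80/60)^(1/3) = 419.9, a change of −0.1 ms.

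Under a model not built to favour it, Fridericia is still nearly flat over this range and Bazett is not.

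**Placebo contrast.** If repolarisation is unchanged and aldesleukin raises rate by 10 bpm with no change on placebo, the expected QTcB difference between arms is the same 9 to 11 ms. Placebo numbers are also small: 2 per dose group, so 5 × 2 = 10 in Part A and 4 × 2 = 8 in Part B.

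**Distance from the Box 1 change limit.** Under the cube-root model, starting at 60 bpm, rate alone reaches +60 ms at 60 × (60/QTcF + 1)^6. That is 139 bpm at QTcF 400 ms and 134 bpm at 420 ms. Extending the assumption to 440 ms gives 129 bpm, and the linear model at 440 ms passes 60 ms near 110 bpm (+61.0). Only a large rise would do it.

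**The case against.** The case against has several parts.

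- **Nothing is misstated.** QTcB is a recognised correction and is used consistently for eligibility, outcome and stopping. A second correction could sit in the full protocol, its supplements or a SAP, none of which is shown. This stands as a limit: the point concerns what the article names. But the article does name a measure, so this is a stated choice and not a detail left blank.
- **The evidence for a rate effect is thin.** A reader might infer that IL-2 at these doses will raise heart rate and so produce apparent QT prolongation. The article does not support that. No section reports a heart-rate rise at low dose. The tachycardia belongs to doses of up to about 120 million IU, some 120/3 = 40 times this trial's cap. No cardiovascular adverse events were noted in the healthy-volunteer or diabetes studies. Influenza-like symptoms occurred in 5.3% of the 38 lupus patients, and the dose-response in the diabetes study is for non-serious events in general. Scheduled post-dose ECGs end at 60 min, whereas the Background puts peak levels at 2 to 6 hours, so a rate effect near the peak may largely miss them. All of this stands.
- **Heart rate and temperature are in the same safety outcome.** Reviewers would see a rate change beside QTcB, the TMG looks at ECGs, and the DMC may ask for further analyses. The analysis is descriptive, with no confirmatory test. This reduces the harm. But seeing both rise does not tell a reader how much of the QTcB change is due to rate, and a second correction does.
- **The likelier error is cautious.** A rate rise makes QTcB over-read. The article offers no mechanism for a rate fall that would mask prolongation. This also stands, although a false dose-related QTc signal would still mislead the choice of dose.
- **Replacing QTcB would break continuity.** Eligibility and Box 1 are on the Bazett scale. This is a good reason to add to QTcB and not to demote it.

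**Conclusion.** The point holds in conditional form. The only QT measure named in the primary safety outcome depends on heart rate if QT varies less steeply with RR than a square root. If aldesleukin raises heart rate, part of a QTcB change by dose, and of its contrast with placebo, could be a rate effect. For cube-root QTc of 400 to 420 ms and a starting rate of 60 to 70 bpm, that part is about 9 to 11 ms per assumed 10 bpm rise and 18 to 21 ms for 20 bpm. Whether any such rise occurs at 0.3 to 3×10^6 IU cannot be told from the article.

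A reader might also infer that the QT stopping criterion would be set off by heart rate alone. The working shows that only large rises would do so, and the point does not bear on that criterion. It is a modest improvement, worth making because it costs almost nothing and concerns a primary safety measure in patients for whom the drug is currently contraindicated.

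**What to change.** In the Outcome measure section, Part A, and by extension the Part B safety endpoint, add QTcF = QT/RR^(1/3), derived from the same ECGs, as a prespecified QT safety summary. Report its change from baseline by dose and against placebo, tabulated beside QTcB and the heart rate from the same ECG. Give both corrections to the TMG, in aggregate so that the blind is kept, and to the DMC.

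Keep QTcB for continuity with Table 1 and Box 1. The eligibility and stopping criteria are not changed.

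The cost is one derived variable and extra table columns. QT and rate can be read from ECGs already scheduled, so no visit, procedure or patient is added.

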#### Part B

As with part A, the primary endpoint will be safety and tolerability of IL-2. A further primary endpoint will be the change in mean circulating Treg levels and whether IL-2 increases mean circulating Treg levels by at least 75% over the 5 days of the treatment period. Exploratory endpoints are the same as for Part A.

### AE reporting

AEs, adverse reactions (ARs), serious AE/ARs (SAEs/SARs) and suspected unexpected SARs will be defined as per the International Conference on Harmonisation definitions. A suitably qualified medical doctor will determine the relationship and causality of each AE to the study drug as either ‘related’ (defined as having a plausible temporal relation and not judged attributable to other causes) or ‘not related’. They will also make an assessment on severity and seriousness. Abnormal or significant changes in laboratory results are only AEs if they are deemed to be of clinical significance or if a medical intervention is required. Whether a patient needs to be withdrawn due to the severity of their AE is left up to the discretion of principal investigator.

### Lymphocyte analysis

Lymphocyte subset analysis will be performed at the Department of Clinical Immunology, Cambridge University Hospitals, Cambridge, UK, within 4 hours of sample collection in EDTA. Laboratory technicians will be blinded to treatment allocation. The antibodies that will be used are anti-CD3 (clone SK7, phycoerythrin (PE)-Cy7 labelled; BD Biosciences), anti-CD4 (clone RPA-T4, fluorescein Isothiocyanate (FITC) labelled; BD Biosciences), anti-CD127 (clone HIL-7R-M21, PE labelled; BD Biosciences), anti-CD25 (clone M-A251 and 2A3, allophycocyanin (APC) labelled; BD Biosciences), anti-CD45RA (clone HI100, APC-Cy7 labelled; BioLegend) and anti-CD62L (clone DREG-56, PerCP/Cy5.5 labelled; BioLegend). Whole blood will be assessed by performing clinical FACS to measure the absolute lymphocyte count, lymphocytes subsets and CD25 expression on Treg cells. Fixed concentrations of fluorescently labelled beads will be added to whole blood to count the absolute number of lymphocytes, CD3^+^, CD4^+^ and CD8^+^ T cells, CD19^+^ B cells and CD19^−^ CD16^+^ CD56^+^ NK. Simultaneous whole blood FACS assay will be performed where a lymphocyte gate is drawn to include all events, while the CD3^+^, CD4^+^ T-cell gate excludes CD8^+^ T cells and B cells. Six standardised beads labelled with different quantities of fluorescent APC are measured by FACS to accurately measure CD25-APC on the surface of Tregs compared with a standardised curve. To minimise interassay variation, mean fluorescence intensity can be read from this curve. Tregs will be defined by CD3^+^CD4^+^CD25^high^CD127^low^ makers and will be separated from non-Tregs and used to calculate the absolute Treg count out of CD3^+^CD4^+^ T cells. Among the non-Treg T effector CD43^+^CD4^+^ population, we will define effector memory cells by CD45RA^−^CD62L^−^ markers, effector memory CD45 RA^+^(TEMRA) cells by CD45RA^+^CD62L^−^ markers, naïve effectors cells by CD45RA^+^CD62L^+^ markers and central memory cells by CD45RA^−^CD62L^+^ markers. Total memory effectors are the sum of central memory and effector memory cells.

